### Collection, preparation, storage and transport of biologic samples

Blood, urine, feces, biopsy tissues, and aspirates will be collected, prepared, preserved, and transported according to the standard operating procedures prepared for this protocol. Samples will be collected at the time points aforementioned.

Community health workers (CHWs) will be responsible for the collection of fecal and urine samples (Additional file 1: Figure S1). Urine samples will be aseptically collected into 100 mL pediatric urine collector bags using a suprapubic tap, 2 mL of urine will be aliquoted in a 4.5 mL cryovial and stored at -2 °C or -8 °C during transport to the Matiari lab and then to the Pediatric Infectious Diseases Research Laboratory (IDRL) at AKUH, once at the IDRL the urine samples will be stored at − 80 °C.

Fecal samples will be collected and cryopreserved within 30 min of production and then transported to the Matiari lab. At the lab, cryovials will be placed into a -80 °C freezer prior to shipping on dry ice to Washington University in St. Louis (WUSTL), USA. Approximately 1 g of fecal material per unique sample/time-point is required. No additives, preservatives or media will be added to the fecal samples.

For blood samples, trained phlebotomists will collect 3-5 mL of venous blood in a labeled blood collection tube (neutral vacutainer tube) after following all aseptic precautions. After collection, the labeled tube will be held upright in a test tube rack for 30 min to allow the blood to clot at room temperature. Each sample will be centrifuged for serum separation and then after successful separation will be pipetted into labeled cryovials. This initial processing will be done at our field site research lab. The vials will be stored in a cooler maintained at 2-8 °C during transportation to the Pediatric IDRL at AKUH, where they will be stored at − 80 °C freezers.

Screening for celiac disease will be performed via testing for serum TTG-IgA. We will also screen for the most important determinant of genetic susceptibility for celiac disease i.e. the presence of human leukocyte antigen-DQ (HLA-DQ) heterdimers DQ2 and DQ8 using Genome Wide Association Studies (GWAS). For participants undergoing UGI endoscopy, gastric biopsies (from the antrum and body) will only be obtained at the discretion of the pediatric gastroenterologist performing the endoscopy. These biopsies will be microscopically assessed for *Helicobacter pylori* associated gastritis on hematoxylin and eosin (H&E) stain, and a duodenal biopsy will also be microscopically assessed for the presence of *Giardia* on H&E stain. The plan for the biopsy workup is detailed in Table 3.

### Environmental enteric dysfunction biopsy initiative (EEDBI) consortium and EE score

The EEDBI Consortium [32] has been assembled from Bill and Melinda Gates Foundation EE biopsy funded projects with cohorts in Zambia [33], Bangladesh [34], and Pakistan. Recently a preliminary EE score, which incorporates acute and chronic inflammation, the presence of inflammatory cells, villus architecture, secretory cells, enterocyte injury, and epithelial detachment, is under development by the consortium, and a preliminary construct was used in our Phase 1 work [22]. The final biopsy scoring system is being developed by a team of pathologists and will be an extension of this preliminary scoring system. We will be using this score on our duodenal biopsies to assess the spectrum of EE.

### Biomarkers

In our Phase 1 work, we noted significant associations between several biomarkers and longitudinal Z scores for subsequent child height and weight  [17, 21, 26]. These biomarkers in addition to an expanded biomarker panel have been selected to test for intestinal barrier structure and function in SEEM. Data will be collected in a longitudinal fashion; monthly anthropometric measurements over 18 months, and biomarker assessment at the aforementioned time points. The biomarkers to be tested in blood and feces are listed in Table 2.

### Fecal calorimetry

In those children who undergo endoscopy at AKUH, fecal calorimetry (6200 Isoperibol Calorimeter; Parr Instrument Company, Moline, IL, USA) will be performed to obtain macronutrient specific determination of fecal energy [35]. Total protein, fat, and carbohydrate energy content of a single fecal aliquot will be compared against the child’s clinical phenotype (including severity of wasting), fecal and duodenal enteropathogen burden, endoscopic inflammation, and histologic severity.

### Fecal intestinal epithelial cells

Isolation and characterization of intestinal epithelial cells (IEC) from feces as a “liquid biopsy” for epigenetic-based detection of colorectal cancer has become an area of intense study [36, 37]. We have adapted these emerging technologies to EE, such that the isolation and preservation of exfoliated IECs from fecal specimens (fecal samples taken at 3–6 and 9 months, and additionally from children undergoing UGI endoscopy 48 h prior to the procedure) is currently in process to allow for assessment of targeted IEC DNA methylation as a function of age, growth, microbiome and enteric illnesses.

### Lactose/Rhamnose (L:R) test

The L:R test is a promising functional test that reflects gut permeability and absorptive capacity [38, 39]. This test is currently being validated in multiple field settings via the EEDBI Consortium [40] and has shown to be more advantageous compared to the lactulose/mannitol test (more often reported dual sugar permeability test in the past two decades) due to lack of pre-dose urinary rhamnose in comparison to mannitol which is used as an inactive ingredient in some oral vaccines and in foods [41]. Dual sugar permeability testing has been used as a surrogate marker of EE [42, 43]. Since our study provides an objective, histology-based diagnosis of EE, we will perform the L:R test in all children (malnourished as well as healthy controls) at approximately 13 months of age. The goal of this is to assess in children who fail to respond to nutritional intervention, whether this failure is associated with an alteration in their intestinal permeability. We will then correlate the findings of the L:R test with the histology of UGI mucosa in malnourished children.

### Gut microbiota/microbiome

Recent work that combines (i) culture-independent analyses of fecal samples collected from healthy members of birth cohorts living in Bangladesh and Malawi with (ii) machine learning algorithms have defined a normal program of gut microbial community development [44–46]. This program is manifested by temporal changes in the representation of ‘age-discriminatory’ bacterial strains. Applying this microbial signature of normal community assembly (maturation) to children diagnosed with severe acute malnutrition (SAM) revealed that their microbiota appear younger than those of their chronologically age-matched healthy counterparts living in the same locale [44, 45]. Moreover, transplantation of microbiota from healthy and undernourished children into young germ-free mice has provided preclinical evidence that gut microbiota immaturity is causally related to many of the manifestations of undernutrition [44–46].

To date, studies of the role of the gut microbiota in the pathogenesis of environmental enteropathy (EE) have been limited by challenges in obtaining well-preserved upper GI communities from individuals whose disease status has been confirmed by endoscopic evaluation. To define the relationship between the configuration of the fecal microbiota and histopathologically-defined EE in the SEEM cohort, we will first generate Random Forests-derived models of normal gut microbial community development; this will be done using bacterial V4-16S rDNA and shotgun sequencing datasets of community DNA respectively, generated from monthly fecal samples collected for the first 2 years of life from well nourished children (WHZ > 0 and HAZ > -1) of the Matiari birth cohort. These culture independent methods will be applied to duodenal biopsies and aspirates collected at endoscopy from children who failed to respond to nutritional intervention in order to identify bacterial strains (and members of other domains of life and their viruses) in the proximal small intestine whose representation/abundance are correlated with severity of EE (as assessed by histologic grading [22]). Bacterial strains will be cultured and their genomes sequenced. BugFACS [47] will also be performed on fecal samples obtained from children at the time of endoscopy to identify bacterial strains whose targeting by mucosal IgA is correlated with pathologic features of disease. These results will be further contextualized using data obtained from (i) multi-omics analysis of duodenal specimens from the same children that will be performed at CCHMC and WUSTL (RNA-Seq, metabolomics/proteomics), plus (ii) results of EE biomarker analyses performed on contemporaneously collected plasma and fecal specimens.

A follow-on component of this work will involve transplantation of duodenal microbial community members collected from children with varying degrees of EE severity into germ-free mice fed a prototypic diet consumed by children living in Matiari. The objective will be to test the hypothesis that these communities transmit enteropathy to recipient animals and the relationship between enteropathy features and growth faltering/undernutrition. These assessments include measurements of (i) lean body mass gain (quantified by whole body magnetic resonance), (ii) bone growth (measured by micro-computed tomography and by serum biomarkers of osteoblastic and osteoclastic activity), (iii) gut barrier function (histochemical and immunohistochemical markers such as EpCAM, claudin-2/− 4, tight-junction protein-1, functional assays such as Fluorescein Isothiocyanate (FITC)-labelled dextran permeability, transcriptional (RNA-Seq)/proteomic analyses of different gut segments, and (iv) immune phenotypes (FACS sorting of intestinal and extra-intestinal tissues). If preclinical proof of concept is established for a causal role of the small intestinal microbiota in the pathogenesis of EE, these gnotobiotic models will permit a search for key effector microbes, the mechanisms through which they operate and ultimately tests of therapeutic concepts.

### Histopathologic, immunohistochemistry and transcriptomic work up of biopsy specimens

We hypothesize biopsies from children whose endoscopic workup does not reveal a clear malabsorptive pathology, such as celiac disease, will likely demonstrate advanced features of EE. Previous studies suggest at least two factors contribute to EE: (i) chronic T-cell mediated intestinal damage and (ii) perturbations in microbial community structure/function [13, 48]. Recognizing that our sample will be restricted to children whose wasting (WHZ ≤ − 2) is refractory to nutritional intervention, we will comprehensively assess biopsy specimens to better understand the pathology of the proximal small intestinal mucosa in EE.

One such previous attempt utilizing duodenal biopsies compared malnourished children in Gambia with healthy UK age-matched children to better understand the pathogenesis underlying this disorder [10]. This study was, however, restricted to morphometric and targeted immunohistochemical analyses for immune cell markers, and did not investigate gene expression associated with the absorptive epithelial layer more broadly. The authors concluded that cell-mediated Th1 response might impair mechanisms of oral tolerance and drive progressive growth failure despite intensive nutritional intervention [10]. Therefore, we propose to supplement routine clinical histologic morphometric analyses with (i) targeted staining to characterize immune cells and the epithelial layer (working with the UVa Biorepository and Tissue Research Facility (BTRF) we have recently established a protocol for triple color immunohistochemical staining), (ii) RNA-Seq analyses to capture a more inclusive EE gut gene expression signature, (iii) gut biopsy DNA-based 16S rDNA characterization of the biopsy-adherent bacterial communities, and (iv) perform microbe:gene association studies (Fig. 3). We hope that these data will provide new insights into both disease pathogenesis and treatment, as well as gut-derived circulating biomarkers for disease severity, which may be assayed in future studies using the banked sera from the larger 400 patient SEEM cohort.

**Fig. 3 Fig3:**
[figure not shown]
SEEM transcriptome/genetics/biomarkers/microbiome framework at the time of endoscopy. **a** Is a detailed description of how samples will be collected throughout the study process from the birth cohorts; **b** Shows the groups, samples, and planned analyses at the time of endoscopy. Note for **a**: *WHZ* Weight-for-Height Z score, *RF * Random Forest, *EGD* Esophagogastroduodenoscopy, infants* = 0 — 3 months old. Note for **b**: *SEEM* Study of Environmental Enteropathy and Malnutrition, *CCHMC* Cincinnati Children’s Hospital Medical Center, *IBD* Inflammatory Bowel Disease, *CBC* complete blood count, *CRP* C-Reactive Protein, *EE* Environmental Enteropathy, * = with a preference to enroll children under 5 years of age

Recently, RNA-Seq and 16S rDNA characterization has been employed to characterize the global pattern of ileal gene expression and the ileal microbial community in treatment-naïve pediatric patients with Crohn’s disease, disease controls with ulcerative colitis, and healthy control individuals. [27] This was followed by a previously established multivariate approach (MaAsLin) [49, 50] to test for associations between selected genes and the microbial taxa. The resultant analyses showed a significant association between expression of components of the APOA1 module and specific *Firmicutes* and *Bacteriodetes* [27].

Furthermore, a multivariate analysis which included disease severity and treatment exposures, showed that Crohn’s patients with the greatest reduction in APOA1 expression at diagnosis were the least likely to achieve clinical remission with current therapies. This suppression of the anti-oxidant lipoproteins in Crohn’s could hence serve as a potential target for future therapies [27].

Similar to the above findings in Crohn’s patients, gene expression studies of duodenal biopsies comparing age-matched controls and celiac patients likewise demonstrate reduction of APOA1 coupled with induction of IFN_γ_ [28]. Together with results described by Campbell et al. [10] showing induction of IFN_γ_ expressing T cells in children with EE in Gambia, these data suggest that this IFN_γ_/APOA1 gene co-expression signature may represent a common pathway of chronic small bowel inflammation and malnutrition.

We plan to test this novel concept by including analysis of duodenal gene expression from disease controls with celiac disease and Crohn’s, together with healthy age-matched controls enrolled at CCHMC. This will provide critical insight into shared and unique features of host epithelial and immune pathogenesis, relative to what are likely to be distinct microbial shifts, across these three disorders in undernourished Pakistani and US children. We anticipate that the induction of IFN_γ_ in EE will in turn be associated with a reduction in apolipoproteins and enterocyte lipid metabolism pathways similar to Crohn’s [27], and celiac disease [28]. Different types of APOA1 interventions are in pre-clinical development for atherosclerosis and inflammatory bowel disease. If we identify a reduction in APOA1 and associated enterocyte lipid metabolic pathways in EE, such treatment may benefit children with EE as well.

### Data analysis plan

This study will result in a vast dataset containing sociodemographic and anthropometric information, as well as biomarkers found in urine, stool, and blood, and endoscopic biopsy results highlighting histopathologic features of both diseased and healthy gastrointestinal tracts.

The WHO Child Growth Standards (WHO Anthro, Geneva, Switzerland) [51] will be used to calculate z-scores, and assess growth both as continuous measures of height-for-age z-score (HAZ), weight-for-age z-score (WAZ) and weight-for-height z-score (WHZ); and as categorized variables of stunting as HAZ < − 2 SD (standard deviation), underweight as WAZ < − 2 SD and wasting as WHZ < − 2 SD. Participant descriptive statistics will be presented as means (standard error, SE) and as frequencies (percentages) for continuous and categorical outcomes, respectively. We will also perform simple linear regression for a specific time point and mixed-effects modeling analysis for repeated measurements to study change in growth trends over the follow-up period.

Mass spectrometry will be used to determine serum and urine bile acid profiles and serum non-essential fatty acid levels, and amino acid profiles. In addition, the cellular fraction of the obtained blood will be utilized for DNA extraction and high-throughput genotyping using Infinium HumanOmniExpressExome [52]. Genotyping will also be used to determine HLA typing of the individual and their associated genetic ethnicity. Given the similarities between EE and celiac disease, it will be of interest to determine whether there is also a common HLA genotype associated with EE [53]. Both environmental and genetic factors [54], play roles in gut microbial composition, therefore, we will control for genetic variants (i.e. HLA [55], FUT2 [56]) in some of the planned microbial and gene expression analyses.

We will use a variety of computational/statistical approaches to assess the extent to which expression of various genes and their associated metabolic/signaling pathways in duodenal biopsies in children with celiac disease, Crohn’s disease, and EE overlap or differ. We will approach this using several statistical methods; PCA plots; Venn diagrams of the differently expressed genes between celiac disease vs. controls, EE vs. controls, and Crohn’s disease vs. controls; and associated pathway analyses. A significant overlap in pathways could provide insights into pathogenesis and new treatment approaches, such as tight junction modulation, which are in development for celiac disease [57]. Gene signatures distinct for EE would further provide a promising source of future therapeutic targets and initial tissue-level validation of promising biomarkers that would be useful for predicting growth and powering studies to test future interventions against EE. We also plan to compare proximal small intestinal duodenal biopsies with distal ileal biopsies in the Crohn’s cohort to determine how well the duodenal pattern of gene expression reflects the ileum.

Analyses of biopsies from both Crohn’s disease and celiac disease patients will also provide us the opportunity to test for the relationship between the microbial community and gene expression signatures. We will test for associations between taxa of the duodenal microbial community and specific clinical and gene expression metadata using Multivariate Analysis by Linear Models (MaAsLin) as has been described in prior studies [27, 49, 50]. A comprehensive description of this analysis method has been published online [58]. In short, for each arcsine square root transformed microbial feature, a model is selected from metadata using gradient boosting (gbm package [59]). Covariates in the selected model are then evaluated controlling for potential confounders using a general linear model. Additionally, confounders will also be assessed via construction of a causal pathway. Multiple comparisons over factor levels will be adjusted using a Bonferroni correction, and multiple hypothesis tests over all clades and metadata will be adjusted with a false discovery rate [60].

All significant (α < 0.05) associations will be investigated in the analysis: clinical phenotype (including severity of wasting), stool and duodenal enteropathogen burden, endoscopic inflammation, histologic severity, and selected duodenal differentially expressed genes such as IFN_γ_ and APOA1. We plan to control for age, gender, and body mass index (as a measure of nutritional status) in our analysis. These analyses will identify specific duodenal microbial taxa associated with differences in IFN_γ_ and/or APOA1 gene expression across the three disorders tested; EE, Crohn’s disease, and celiac disease.

Next, analyses of mRNAseq performed on biopsy tissues will be carried out using polyA-RNA selection, fragmentation, cDNA synthesis, adaptor ligation, and library preparation with TRUSeq RNA Sample preparation (Illumina, San Diego, CA, USA). Paired-end 75 bp sequencing will be performed using the Illumina HiSeq 2000 in the CCHMC NIH-supported Digestive Health Center with a minimum depth of 20 million reads per sample. Reads will be aligned using TopHat [61]. The aligned reads will be quantified by Avadis NGS software (Version 1.3.0, Build 163,982 Strand Scientific Intelligence, Inc., San Francisco, CA, USA) using Hg19 as the reference genome and RPKM as an output. The DESeq algorithm will be used for RPKM normalization within Avadis NGS software. Two more recently applied alternative approaches for quantification will also be assessed using kallisto [62] and eXpress [63].

For RNA-Seq expression and gene enrichment analysis samples will be stratified into specific clinical subgroups including control, EE, celiac disease, and Crohn’s disease. For some analyses the EE group will be further sub-divided into those with an identified infection (e.g. *Giardia, H. pylori*) and those without an identified infectious etiology. In addition, we plan to stratify the Crohn’s patient samples by their location to assess expression differences between proximal (duodenal) and distal (ileum) small bowel expression.

Other potential sub-stratification of the EE group will be based on CRP level, histologic severity, response to rotavirus infection (by measuring rotavirus IgA levels), and weight/height outcomes. Differentially expressed genes of the above stratified groups will be determined by the Audic Claverie method using the Benjamini-Hochberg false discovery rate correction (FDR 0.05) and analyzed for fold change differences. Normalized intensity values will be used for patterns of gene expression. Pearson correlation based on trend and rate of change will be performed for IFN_γ_ and APOA1 gene expression across defined groups for correlation coefficient of 0.98 < |r| < 1.

ToppGene [64], ToppCluster [65], and IPA (Ingenuity Systems) software will be used to test for functional annotation enrichment analyses of upstream regulators, immune cell types, pathways, phenotype, and biologic functions. Functional annotation enrichment analyses for immune cell type enrichments will be characterized using the Immunological Genome Project data series through ToppGene. Visualization of the functional networks will be obtained using Cytoscape v.3.02 [66].

Lastly, an anticipated challenge in interpreting clinical biopsies from EE and celiac disease will be the possible histopathological overlap between these distinct but related enteropathies [10, 22]. In light of this, we propose to use duodenal biopsy data (converted to whole slide images using Leica SCN400 slide scanner [Meyer Instruments, Houston, TX] and Olympus VS120 Virtual Slide Microscope [Olympus Corporation Inc., Center Valley, Pennsylvania]) from EE, celiac disease and normal healthy biopsy from patients recruited in SEEM and archival duodenal biopsies from the UVa BTRF as data input for a deep learning image analysis algorithm. Deep learning, or machine learning, has been said to be the natural extension to our current statistical analysis [67] especially in the context of multiomic data as in SEEM, and is at the forefront of advances in both technology and medicine [68]. We will use a subtype of deep learning known as Convolutional Neural Networks (CNNs) [69], to detect morphological distinguishing histological features between disease phenotypes. We will also couple our CNN layers with a deconvolution layer [70, 71], and a Gradient Class Activation Map layer [72], which will allow us to trace back high activation features to the corresponding biopsy. This will allow us to enhance the detection of pathologic morphological features that can help distinguish between celiac disease and EE, both when compared to each other and also when compared to healthy duodenal tissue. Furthermore, in addition to applying the EEDBI scoring system, we will use this deep learning driven approach to correlate high activation features to identify multiomic patterns not identified by traditional pathology scoring.

The overall schedule for enrolment, interventions and assessments, including UGI endoscopy and biopsies, is described in Fig. 3; and the data transfer between each collaborating institution is outlined in Fig. 4. To ensure optimal outcomes from this ambitious undertaking, we designed SEEM with monitoring and quality control measures, timelines for milestones, anticipation of challenges, and consideration of ethics and data dissemination.

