
## Methods

SEEM Pakistan is a multi-institutional collaboration between the Aga Khan University Hospital (AKUH), Pakistan, University of Virginia (UVa), Cincinnati Children’s Hospital Medical Center (CCHMC) and Washington University in St. Louis (WUSTL) in the USA, with funding by the Bill and Melinda Gates Foundation (2016 through 2019). Enrollment has been completed and a cohort of 400 children has been established (350 malnourished children and 50 well-nourished healthy controls).

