### Study settings and participants

The basic framework for the SEEM Pakistan study is described in Figs. 1 and 2. The Department of Paediatrics and Child Health at AKUH has an established field site at Matiari, Pakistan, which is a rural district about 3 hours drive north of Karachi, Pakistan. We anticipated enrolling 350 children from ages 0 to 6 months with weight for height Z score (WHZ) < − 2 at the time of enrollment. We also anticipated enrolling 50 children of the same age with healthy ponderal and linear anthropometric assessments based on consistent WHZ > 0 and height for age Z score (HAZ) > − 1 on two consecutive visits between 3 to 6 months, to serve as healthy controls. Administration of routine rotavirus vaccine will be facilitated as a part of our study, and other Expanded Program on Immunizations (EPI) vaccines will also be facilitated as part of other ongoing research activities.

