### Sample size

Participants will be recruited from our prospective cohort. Based on our phase 1 cohort [14], we anticipated that the cohort of 50 SEEM patients, with duodenal samples collected by endoscopy, will include at least 20 without a single identified treatable infection, i.e. identified *Giardia* or *H. pylori* infection*.* The primary endpoint guiding our sample size estimate will be the anticipated differences in duodenal IFN_γ_ and APOA1 gene expression between subjects with EE and healthy controls. We anticipate that induction of IFN_γ_ gene expression will be associated with a reduction in APOA1 gene expression as per a recent study on Crohn’s disease [27] and that of Bragde et al. on celiac disease [28]. In the Crohn’s study, the mean (SD) Reads Per Kilobase per Million Mapped reads (RPKM) IFN_γ_ gene expression at diagnosis was equal to 1.86(2.7) in patients with Crohn’s, and 0.33(0.38) in healthy controls. The mean (SD) RPKM APOA1 gene expression at diagnosis was 927(1469) in patients with Crohn’s, and 3012(3080) in healthy controls. We anticipate similar differences between EE and healthy controls in our study. Based on these results, 30 healthy controls and 25 EE subjects without a specific treatable infection will provide 90% power to detect such a difference with α = 0.05. The secondary endpoint will be to perform an undirected analyses to capture the overall gene and signatures that are different between described groups. Based on previously published data for RNA-Seq samples size estimation [29], if we estimate a coefficient of variation of counts of 0.4 as was observed in 90% of the genes in a range of human studies, alpha of 0.05 and power of 0.8, a sample size of 20 per group will be needed.

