### Safety measures and preparation for adverse events

One of our major goals was to optimize safety for UGI endoscopies, especially given our LMIC study setting. Although never without elements of risk during the procedure and anesthesia, endoscopy is a very safe procedure when conducted by trained experienced personnel in a well-equipped facility. We have safety data from our own pilot EE phase 1 study in which we successfully performed endoscopy on 11 children with a median (Q1 – Q3) age of 22 (20–23) months (14). There is also data from studies conducted in Gambia [10] where children underwent endoscopy under anesthesia, and Zambia [73] where malnourished children underwent endoscopies with collection of duodenal biopsy samples under anesthesia. Neither of these studies reported any endoscopy-related adverse events during or after the procedures.

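### Participants' continuous data are to be described as mean (SE), which shows how precisely a mean is estimated and not how much children vary; a low-severity reporting correction

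*Protocol article*

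**What the plan says.** The Data analysis plan first sets out how growth Z scores will be calculated and categorised, and then gives the rule for describing participants: "Participant descriptive statistics will be presented as means (standard error, SE) and as frequencies (percentages) for continuous and categorical outcomes, respectively". It names no SD, median, quartiles or range for that purpose. Where SD appears in the same paragraph, it belongs to the cut-offs for stunting, underweight and wasting.

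The Methods section gives the make-up of the established cohort as "350 malnourished children and 50 well-nourished healthy controls". Under Study settings and participants, the malnourished group is defined by WHZ below −2 at enrolment, and the well-nourished group by "consistent WHZ > 0 and height for age Z score (HAZ) > − 1 on two consecutive visits between 3 to 6 months".

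**The concern.** A descriptive table should tell the reader who the children are and how much they differ from one another. The SE answers a different question, namely how far the sample mean may lie from the population mean, and it falls with the square root of the number measured. Two things follow here.

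- Variation between children would appear much smaller than it is in every continuous row.
- The two cohorts differ sevenfold in size, so their printed figures would not be comparable with each other as measures of spread.

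The number measured also changes over follow-up. Under Study settings and participants, blood, urine and feces come from all children at 3–6 and 9 months, but feces at 10 and about 14 months come only from those eligible for nutritional intervention. An SE would move between those time points because n changed, even if the spread did not.

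What is at stake is how readers understand the descriptive tables. The inference is not affected. Because the article states this choice outright, it is not a detail left open for a fuller plan to supply.

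**Working it through.** The article gives no numerical result for this rule, so there is nothing to reproduce. The check is direct arithmetic.

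**Inputs**
- n₁ = 350 malnourished and n₂ = 50 well-nourished children (Methods).
- Planned summary: mean (SE) (Data analysis plan).
- SD of the variable: not given for this cohort, so it is assumed and varied from 0.5 to 1.2 Z-score units.

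**Step 1. How far the printed figure falls below the SD.** SE = SD/√n, so SD/SE = √n.
- Malnourished: √350 = 18.7
- Well-nourished: √50 = 7.1

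These two factors hold whatever the SD is, provided all children in the group are measured.

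**Step 2. How the two groups compare if their SDs are equal.** SE₂/SE₁ = √(n₁/n₂) = √(350/50) = √7 = 2.65.

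**Step 3. What would be printed, by assumed common SD.**

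| Assumed common SD | SE at n = 350 | SE at n = 50 | Ratio |
|---|---|---|---|
| 0.5 | 0.027 | 0.071 | 2.65 |
| 0.8 | 0.043 | 0.113 | 2.65 |
| 1.0 | 0.053 | 0.141 | 2.65 |
| 1.2 | 0.064 | 0.170 | 2.65 |

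**Step 4. If the SDs are not equal.** With r = SD₂/SD₁, the ratio of printed figures is r × 2.65. It is 1.32 at r = 0.5, 1.98 at r = 0.75 and 3.97 at r = 1.5. The two printed SEs would agree only at r = 1/2.65 = 0.38, that is, when the smaller group really varied much less. In every case the ratio shown is 2.65 times the true ratio of spreads.

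**Step 5. After the change.** With mean (SD), two groups whose SD is 1.0 both show 1.0, whatever their size.

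**The case against.** The strongest reply is that this is a matter of table format. The measure is openly labelled as a standard error, so nobody is told that it is spread. With n reported, SD = SE × √n is exact and no information about the mean or SD is lost. Growth will be analysed by linear regression and mixed-effects models, and nothing in those analyses rests on the descriptive table. All of this stands, and it is why the point is graded low. It does not make the SE a suitable description of participants, since it leaves the reader to do the conversion for every row.

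A reader might also infer more than the article supports:

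- **That the two groups do vary equally and the table would misrepresent this.** No cohort SDs are given, and the entry rules differ (WHZ below −2 against WHZ above 0 with HAZ above −1). The 2.65 factor is conditional on equal spread.
- **That widely overlapping groups would be made to look separate.** This is not shown. For enrolment WHZ the groups cannot overlap, by design.
- **That the rule will distort the gene-expression results.** The sentence concerns participant descriptives and follows the anthropometric definitions. RNA-Seq has its own plan (PCA, pathway analyses, differential expression with false discovery rate control). Its samples come from the endoscopy patients and the US controls, so the 350 and 50 do not apply to it.
- **That the article contradicts itself.** The mean (SD) values under Sample size are quoted from an earlier Crohn's disease study, and the median (Q1–Q3) under Safety measures is the age of 11 phase 1 children. Neither sets a reporting rule for this study.
- **That later trials could not be powered.** The remark about powering future studies concerns what EE gene signatures and validated biomarkers might offer. It does not concern the participant tables, and the SD is recoverable where n is given.

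**Conclusion.** The point holds as a low-severity reporting correction. The stated summary is the wrong one for describing participants. It would print a figure 18.7 times smaller than the SD at n = 350 and 7.1 times smaller at n = 50; these factors assume complete measurement and would change with the number actually measured. The 2.65-fold difference between the groups further assumes equal SDs, which the article neither states nor implies. Skew in the blood, urine and stool biomarkers is plausible, but the article reports no biomarker distributions, so the use of medians should depend on the data. No test, sample size, power figure or model estimate is affected.

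**What to change.** Change the one sentence in the Data analysis plan so that continuous anthropometric, sociodemographic and biomarker variables are described by mean (SD), or by median (Q1–Q3) where the distribution is skewed, with n shown for each variable and time point. Keep frequencies and percentages for categorical variables as planned. Reserve SEs, or preferably 95% confidence intervals, for estimated quantities such as differences between groups and growth slopes.

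The cost is one sentence and the matching table shells. No further data are needed and no analysis has to be altered.
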